### Statistical Methods To Be Undertaken

FINAL ANALYSIS:

The clinical utility of ptDNA (ptDNA-positive vs ptDNA-negative), as determined by genomic and methylomic output, will be evaluated in consultation with our study biostatistician ([name]) using the following metrics: sensitivity, specificity, positive-predictive value, negative-predictive value, receiver operator characteristics, Kaplan Meier and Cox regression, against the primary and secondary endpoints. Co-variates in these analyses will be accounted for using hierarchical multi-variate logistic regression algorithms.

Additionally, exploratory analyses will be performed to:

- Compare ptDNA detection rate before (at time of PLC) and after (at time of surgical resection) neoadjuvant therapy.
- Compare ptDNA versus circulating tumour DNA (i.e. plasma) to predict sites and patterns of disease recurrence.
- Compare the cost-effectiveness of genomic vs. methylomic approaches to detect ptDNA to inform translation into clinical practice.
  - Using data collected including admission and discharge dates, length of stay, clinical services provided to each episode of care (e.g. CT, PET, laparoscopy, chemotherapy, radiotherapy, surgery etc.), outpatient follow-up, treating clinical units, estimated unit costs based on diagnosis-related group (DRG) and DRG descriptions, we will calculate the actual cost associated with each patient’s care along their cancer treatment journey. Then at a population level, this will be compared to a hypothetical projected cost based on whether ptDNA status changes clinical management, and whether this cost difference offsets the cost of a ptDNA assay.
- Curate and catalogue actionable molecular targets identified from whole exome sequencing of peritoneal wash fluid to inform future clinical trials.

These analyses will be performed using chi-square tests, Pearson correlations and other qualitative methodologies.

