### Study Endpoints

PRIMARY ENDPOINTS:

- 2-year disease free survival (DFS) (*Objective 1*)

SECONDARY ENDPOINTS:

- *Survival*: 3-year peritoneal DFS, 3-year overall survival (OS), 5-year DFS, and 5-year OS (*Objectives 2 & 3*)
- *Peritoneal lavage cytology status*: present/absent/indeterminant (*Objective 3*)
- *Imaging (CT/PET scans) and endoscopy*: Location of disease recurrence (*Objective 3*)
- *Primary tumour histopathological features*: T-stage, N-stage, grade, lymphovascular invasion, perineural infiltration, histological subtypes, tumour size, and tumour regression grading (*Objective 3*)
- *Cost effectiveness*: accounting for assay performance, direct-costs, technical aspects, clinical impact, and quality-adjusted life years (*Objective 4*)
- *Genomic analysis of ptDNA*: mutant allelic frequency thresholds, presence of actionable therapeutic targets against a registry of clinically proven and experimental therapies (*Objectives 5 & 6*)
- *ctDNA status*: present/absent, mutant allelic frequency threshold (*Objectives 7*)

DEFINITIONS FOR PRIMARY AND SECONDARY ENDPOINTS:

- *Disease recurrence*: recurrence of disease after surgical resection of the primary tumour, in any site, detectable on clinical, endoscopic, and/or imaging investigations.
- *Disease free survival*: Time from date of surgical resection to date of disease recurrence
- *Overall survival*: Time from date of surgical resection to date of death
- *Cancer staging*: T, N and M stage for CT/PET scans and histopathology will be according to AJCC 8^th^ Edition for Gastric and Gastroesophageal Junction Cancers

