# **Statistical Methods**

### Sample Size Estimation & Justification & Power Calculation

POWER JUSTIFICATION:

OMEGCA will have 4 observational cohorts as listed below:

- Group 1: Peritoneal lavage cytology-negative & ptDNA-negative
- Group 2: Peritoneal lavage cytology-negative & ptDNA-positive
- Group 3: Peritoneal lavage cytology-positive & ptDNA-negative
- Group 4: Peritoneal lavage cytology-positive & ptDNA-positive

However, as the primary objective of this study is to evaluate the clinical utility of ptDNA as a biomarker to predict the primary endpoint (2-year DFS) in gastroesophageal cancer patients with no apparent micro-metastatic disease in the peritoneum (using current ‘best practice’ staging methods), we have powered this study to compare groups 1 and 2, as these are the patients with *peritoneal lavage cytology-negative* disease. Accordingly, we deemed a 30% absolute DFS difference at 2 years post staging laparoscopy as clinically significant between groups 1 and 2. This is based on our hypothesis that patients who are ptDNA-positive should by definition have cytology-positive disease, even if this was not detected. The conservative estimate of 2-year DFS in patients who are cytology-positive versus cytology-negative is 40% versus 70%, respectively. Using our pilot data (Figure 3), we anticipate approximately 1 in 8 patients who is cytology-negative will be ptDNA-positive, this means an enrolment ratio of 7 to 1 in groups 1 and 2, respectively. To detect a 30% absolute difference in 2-year DFS between these two groups, we would need to enrol 200 patients with 175 patients in group 1 (ptDNA-negative arm) and 25 patients in group 2 (ptDNA-positive arm) to reach 80% statistical power at an alpha <0.05.

INTERIM ANALYSIS:

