Based on centre volume, the number of participating sites, the number of patients already recruited on 18/211, and accounting for a 30% participant attrition rate, we anticipate to complete patient recruitment in 2 years. We will perform an interim analysis at 1 and 2 years after commencement of recruitment to ensure that the enrolment ratio between groups 1 (cytology-negative/ptDNA-negative) and 2 (cytology-negative/ptDNA-positive) is on-track (*Figure 4*). This will be measured by analysing the proportion of patients who are cytology-negative and ptDNA-positive. If the ratio of ptDNA-positive/cytology-negative is ≥10%, then recruitment of patients will continue to the target of 200. If this ratio is <10%, we will adjust our recruitment strategy accordingly. Additionally, we will perform an interim analysis at 3 years after commencement of patient recruitment (i.e. ≥1-year DFS data) to compare DFS between groups.

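### Covariate adjustment for the Cox and Kaplan-Meier analyses of DFS and OS is assigned to logistic regression, which does not fit time-to-event endpoints

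*Protocol*

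**What the plan says.** Protocol section 8b (Final analysis) evaluates ptDNA status with these metrics: "sensitivity, specificity, positive-predictive value, negative-predictive value, receiver operator characteristics, Kaplan Meier and Cox regression". They are applied to the primary and secondary endpoints together. The next sentence reads: "Co-variates in these analyses will be accounted for using hierarchical multi-variate logistic regression algorithms". The Statistical Methods row of the synopsis says the same. Neither place limits the logistic model to binary outcomes or says that the Cox model will carry covariates.

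Section 4c defines DFS as "Time from date of surgical resection to date of disease recurrence", and OS in the same way to death. The primary endpoint is DFS at 2 years. The secondary survival endpoints are read at 3 and 5 years.

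The only attrition figure is in section 8a, in the paragraph on recruitment and interim analysis: "accounting for a 30% participant attrition rate". It supports the forecast that recruitment will finish in 2 years. Section 7c plans to replace withdrawn participants.

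**The concern.** A Cox or Kaplan-Meier analysis cannot be adjusted for covariates by a logistic model. The two use different data (event times with censoring, against yes/no at a fixed time) and estimate different quantities (hazard ratio, against odds ratio). If the sentence is followed, the unadjusted and adjusted ptDNA effects are on different scales, and a reader cannot tell how much of any change is due to adjustment.

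This matters because the groups are formed by a biomarker, not by randomisation, across 10 to 12 sites. The adjusted estimate is therefore the one that carries the conclusion. Only 25 ptDNA-positive patients are planned, so information is scarce.

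The protocol leaves room for censoring before the landmark:
- Section 7b lets a patient stop clinical data collection while data already collected may still be used.
- Section 5a says only that non-attenders may be contacted.
- The DFS definition counts recurrence alone, so a patient who dies without recurrence before 2 years has no observed 2-year recurrence status.

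**Working it through.** **Inputs from the protocol (section 8a).** 2-year DFS is taken from this statement: "The conservative estimate of 2-year DFS in patients who are cytology-positive versus cytology-negative is 40% versus 70%, respectively". It is used as 70% for group 1 (ptDNA-negative) and 40% for group 2 (ptDNA-positive). There are 175 and 25 patients, alpha is 0.05 (taken as two-sided) and power is 80%.

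**1. The plan's own figure.** Comparing two proportions, 70% against 40%, with 175 and 25 patients:
- Fisher's exact test: 80.9%
- z test, unpooled: 82.3%; pooled: 83.6%
- continuity-corrected: 77.6%

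The stated 80% reproduces as a comparison of proportions with every 2-year status known.

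**2. Unknown 2-year status (assumption).** The protocol gives no rate of loss before 2 years. Assume exponential event times and independent exponential loss reaching a fraction d at 2 years. Per group, with 2-year DFS = S:
- event hazard h = −ln(S)/2; loss hazard c = −ln(1−d)/2
- event-free and known = S(1−d)
- unknown = c/(h+c) × [1 − S(1−d)]
- observed event = h/(h+c) × [1 − S(1−d)]

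At d = 0.30:
- Group 1: h = c, so event = unknown = 0.5 × (1 − 0.49) = 0.255, and event-free = 0.49.
- Group 2: event-free = 0.28, event = 0.518, unknown = 0.202.
- Unknown overall: 175 × 0.255 + 25 × 0.2017 = 49.7 of 200, or 24.8%.

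**3. The two ways a logistic model can treat them.** The true odds ratio is (0.70/0.30)/(0.40/0.60) = 3.50.
- Dropped: DFS 0.49/0.745 = 65.8% and 0.28/0.798 = 35.1%. These are 4.2 and 4.9 points too low. The odds ratio is 3.56.
- Counted as event-free: DFS 1 − 0.255 = 74.5% and 1 − 0.518 = 48.2%. The gap is 26.3 points and the odds ratio 3.14.

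| Loss by 2 years (assumed) | Unknown status | Dropped: DFS | Dropped: OR | Dropped: power (pooled z) | Event-free: gap | Event-free: OR |
|---|---|---|---|---|---|---|
| 10% | 8.2% | 68.8% / 38.5% | 3.52 | 81.4% | 28.8 | 3.37 |
| 20% | 16.5% | 67.4% / 36.9% | 3.54 | 78.6% | 27.6 | 3.25 |
| 30% | 24.8% | 65.8% / 35.1% | 3.56 | 75.2% | 26.3 | 3.14 |
| 40% | 33.3% | 63.8% / 33.0% | 3.58 | 70.9% | 24.9 | 3.04 |

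The shape of the loss matters little. With 30% lost uniformly over 2 years, dropping gives 65.5% and 34.8%, and counting as event-free gives 74.2% and 47.6% (gap 26.6).

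**4. Logistic against Cox on the same data.** 1,500 simulated data sets at 30% loss, with ptDNA as the only covariate:
- Logistic, unknowns dropped: power 73.7%
- Logistic, unknowns counted as event-free: power 74.3%
- Cox, all 200 patients: power 80.3%; mean log hazard ratio 0.94, equal to the true ln(2.57) = 0.94, where 2.57 = ln 0.4/ln 0.7

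The Monte Carlo error of each power is about 1 point: √(0.8 × 0.2/1500) = 0.010. Schoenfeld's formula gives a lower Cox power (65.8% at 30% loss). It assumes that 1/8 of events fall in group 2, whereas here 25 × 0.518 = 13.0 of 44.6 + 13.0 = 57.6 events do (22%). The paired simulation is therefore the fairer comparison.

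**The case against.** The strongest reply is that logistic regression is not out of place in this study. The primary endpoint is read at a fixed 2 years and the sample size is a comparison of proportions. Cytology, the histopathological features and the diagnostic metrics are binary or categorical. Cox regression is named, so a method that handles censoring is already planned. Follow-up runs 5 years after the last enrolment (section 5a), so there is almost no administrative censoring before 2 years. Missed visits may be covered by telephone or video, and section 13 asks centres for more than 90% data completeness.

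Most of this stands, and it limits the size of the problem. Where 2-year status is complete, a logistic model is usable. It does not remove the mismatch: the sentence covers all the listed analyses, including Cox and Kaplan-Meier, and the 3- and 5-year endpoints leave more time for loss.

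A reader might also infer that the plan expects 30% loss to follow-up, so that a quarter of patients drop out of the adjusted analysis and its result is biased. The documents do not support that. The 30% belongs to the recruitment forecast, has no time pattern, and is not described as loss of DFS follow-up. Withdrawals are to be replaced. Even if 30% loss is assumed, dropping the unknowns moves the odds ratio only from 3.50 to 3.56. The protocol nowhere proposes counting censored patients as event-free.

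Nor does the protocol say that sensitivity, specificity or ROC will come from tables that ignore censoring. How they are computed is a matter for the statistical analysis plan.

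**Conclusion.** The point holds as a method mismatch. Section 8b and the synopsis assign covariate adjustment of time-to-event analyses to a model that cannot use censored time, which puts the adjusted ptDNA effect on a different scale from the unadjusted one. That much follows from the text alone.

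The numerical cost is conditional. At an assumed 30% independent loss by 2 years, complete-case logistic regression gives about 74% to 75% power against 80% for Cox, with absolute DFS 4 to 5 points too low and the ptDNA odds ratio almost unbiased. At 10% loss the cost is small. These figures assume exponential times, proportional hazards, loss unrelated to prognosis and no other covariates. Informative loss could produce more bias, but the protocol gives nothing from which to size it. The change should be made, but the mismatch does not invalidate the design.

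**What to change.** In section 8b and the synopsis, replace the covariate sentence with one stating that adjusted analyses of DFS and OS use multivariable Cox regression, with site handled by stratification or a shared frailty, and that hierarchical logistic regression is kept for truly binary outcomes such as histopathological features and cytology.

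The cost is one sentence in each place. It needs no new data, no change to sample size and only standard software. Making the change before outcomes are analysed also avoids a later choice between two adjusted models.

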# **Study Design**

### Study Type, Design, Schedule & Methodology

STUDY TYPE:

- Prospective non-interventional cohort study
- This study will include a cohort of patients who have undergone identical biospecimen collection, clinical treatments, and follow-up from Project No: 18/211, entitled ‘*Improving outcomes in gastroesophageal cancer*’ (HREC/44873/PMCC-2018)

ABOUT PROJECT NO: 18/211:

- Relevant to this study, project No: 18/211, entitled ‘*Improving outcomes in gastroesophageal cancer*’ (HREC/44873/PMCC-2018) was in part (as it was multi-facetted with different aims), a multi-centre biospecimen (tumour and normal tissue, blood, and peritoneal fluid) and clinical data collection project.
- Project 18/211 established the collaborative research network and generated the critical pilot data (11 patients) for this proposed study. The patient cohort recruited through Project 18/211 are identical to this proposed study.
- To avoid wastage of patient samples, research cost, human resources, and time, we propose that eligible patients who have undergone identical biospecimen collection, clinical treatments, cancer surveillance and follow-up in Project 18/211 as this proposed study, to be combined for the purpose of data analysis.

STUDY PERIOD:

- Participant recruitment: 2 years
- Clinical follow-up: Follow-up for 5 years after the last enrolled patient

STUDY SAMPLE SIZE:

- Merging of participants from this study and Project No: 18/211
- Combine total participant ≥200 based on power calculation, please see below and in section 8.

STUDY POPULATION:

- All patients with gastroesophageal junction and gastric cancer
- ≥ 18 years-of-age
- Without distant organ, non-regional nodal or gross peritoneal metastases
- Undergoing staging laparoscopy with peritoneal lavage cytology (PLC)
- Undergoing curative-intent treatment (either upfront surgery or chemo/radiotherapy and surgery) for their cancer

DESIGN SUMMARY TO ACHIEVE OBJECTIVES:

- This prospective, multicentre observational cohort study will enrol patients undergoing PLC and subsequent curative-intent treatment for gastroesophageal cancer.
- Tumour and normal (stomach and oesophagus) tissue biopsies, blood, and peritoneal lavage fluid will be collected during pre-treatment staging for all patients.
- A subset of patients (those who undergo neoadjuvant chemo/radiotherapy) will have tumour tissue, blood and peritoneal lavage fluid collected at surgery.

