*Tumour-informed genomic analysis*: Tumour tissue and peritoneal fluid will be sent to the Johns Hopkins University Hospital, Kimmel Cancer Centre, USA (Collaborator: [name]), and plasma DNA will be sent to Haystack Oncology^Pty Ltd^, USA, both for genomics analysis. Tumour specific mutations will be identified via whole exome sequencing of the primary tumour DNA and screened against blood derived buffy coat DNA to exclude germ-line mutations. This will inform targeted mutation assays to be performed on DNA derived from peritoneal lavage fluid and plasma, resulting in a binary output of positive or negative for the presence of ptDNA and ctDNA, respectively.

*Tumour-agnostic methylomic analysis*: Tumour tissue, plasma and peritoneal fluid will undergo methylomic sequencing and analysis at the Peter MaCallum Cancer Centre, through the Translational Genomics Core Facility (Collaborator: [name]). Characteristic tumour methylation markers, consisting of the top differentially methylated regions between gastroesophageal cancer vs. adjacent normal tissue^22^ will be quantified using Methyl-seq.^23^ DNA derived from peritoneal lavage fluid will be sequenced to identify these methylation markers, resulting in a binary output of positive or negative for the presence of ptDNA.

SURVIVAL ENDPOINT DETECTION:

All patients will undergo routine clinical, endoscopic and imaging surveillance as per their local hospital guidelines and practice. This is typically as per the following timelines:

| **Time post-surgery** | **0-1 year** | **1-3 year** | **3-5 year** |
| --- | --- | --- | --- |
| **Clinical** | 3 monthly reviews | 6 monthly reviews | Annual reviews |
| **Imaging CT and/or PET** | At 1 year | Annually | Annually |
| **Endoscopy** | At 1 year | At 2^nd^ and 3^rd^ year | - |

CLINICAL ENCOUNTERS & SPECIMEN COLLECTION:

The table below highlights study-specific clinical encounters of patients, biospecimen collection, and data entry timepoints.

| **Clinical Schedules** | **Timing (location) of assessments/procedures**  **Assessment/Procedure** | **Pre-surgical visits**  **(Clinic)** | **Staging Laparoscopy**  **(Theatre)** | **Surgical Resection**  **(Theatre)** | **Post-operative**  **follow-up**  **(Clinic)** | **Long-term follow-up**  **1-5 years**  **(Clinic)#** |
| --- | --- | --- | --- | --- | --- | --- |
|  | **Informed Consent** | **X** | Reaffirm |  |  |  |
|  | **Demographic data** | **X** |  |  |  |  |

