|  | **Clinical data** | **X** | **X** | **X** | **X** | **X** |
|  | **Histopathological data** |  |  |  | **X** |  |
|  | **CT and PET data** |  |  |  | **X** | **X** |
|  | **Endoscopy data** |  |  |  | **X** | **X** |
|  | **Blood collection** |  | **X** | **X** | **X^** |  |
|  | **Tissue biopsies collection** |  | **X** |  |  |  |
|  | **Peritoneal lavage collection** |  | **X** | **X*** |  |  |
|  | **Survival/recurrence data** |  |  |  |  | **X** |

**X:** designates when such data is generated and is captured as part of this study. ***** Only applicable to participants who undergo neoadjuvant therapy. **^** Where possible. **#** timepoints as per SURVIVAL ENDPOINT DETECTION table above.

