**Addition to standard-of-care procedures**

| **Clinical Schedules** | **Timing (location) of assessments/procedures**  **Assessment/Procedure** | **Staging Laparoscopy**  **(Theatre)** | **Surgical Resection**  **(Theatre)** | **Post-operative**  **follow-up**  **(Clinic)** |
| --- | --- | --- | --- | --- |
|  | **Research blood collection** | **X** | **X** | **X** |
|  | **Research normal and tumour tissue biopsies** | **X** |  |  |
|  | **Research peritoneal lavage collection** | **X** | **X*** |  |

* Only applicable to participants who undergo neoadjuvant therapy.

- *Research blood collection*: 20-30 ml of peripheral blood will be collected prior to skin incision or in outpatient setting.
- *Research normal tissues biopsies*: 4-6 endoscopic biopsies of normal gastric and oesophageal mucosa
- *Research primary tumour biopsies*: 8-12 endoscopic biopsies of primary tumour
- *Peritoneal lavage fluid collection*: 150-250 ml of 500 ml 0.9% saline following 4 quadrant lavage of the abdominal cavity

STANDARDISING PERITONEAL LAVAGE COLLECTION AT STAGING LAPAROSCOPY:

During staging laparoscopy, there is currently NO standardised practice of performing peritoneal lavage. Between centres, there is variability with respect to the volume of saline (typically range from 0 ml to 1 L) applied and the quadrants of the abdomen (typically range from upper 2 quadrants to 4 quadrants) that are washed. Additionally, the pathology department within each hospital typically process and analyse variable amounts of submitted peritoneal lavage fluid. The remainder of this fluid is discarded. Therefore, in this study, we will standardise peritoneal lavage at staging laparoscopy to 500 ml 0.9% saline wash of all 4 quadrants of the abdomen. From this 300 ml will be submitted to anatomical pathology for routine processing and cytological analysis, and 200 ml will be used for ptDNA detection and analysis.

STANDARDISING PERITONEAL LAVAGE COLLECTION AT SURGICAL RESECTION:

For patients who have undergone neoadjuvant therapy, a further peritoneal lavage will be performed at surgical resection. Peritoneal lavage will be performed as soon as possible after achieving peritoneal access (either laparoscopically or via laparotomy). This will involve 500 ml 0.9% saline wash of all 4 quadrants of the abdomen. From this 200 ml will be used for ptDNA detection and analysis. The remaining 300 ml will be discarded.

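### Section 8b names chi-square tests and Pearson correlations for within-patient exploratory comparisons (ptDNA before versus after neoadjuvant therapy; any head-to-head of ptDNA with plasma ctDNA), and names no paired method

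*Protocol*

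**What the plan says.** Section 8b lists four exploratory analyses. The first is: "Compare ptDNA detection rate before (at time of PLC) and after (at time of surgical resection) neoadjuvant therapy". The second is: "Compare ptDNA versus circulating tumour DNA (i.e. plasma) to predict sites and patterns of disease recurrence". The other two are a cost-effectiveness comparison and a catalogue of drug targets. One sentence gives the methods for all four: "These analyses will be performed using chi-square tests, Pearson correlations and other qualitative methodologies".

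The sampling scheme shows who contributes to the first two.

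- Staging samples, section 5a: "blood, and peritoneal lavage fluid will be collected during pre-treatment staging for all patients".
- Samples at resection, section 5a: "A subset of patients (those who undergo neoadjuvant chemo/radiotherapy) will have tumour tissue, blood and peritoneal lavage fluid collected at surgery". The footnote to the encounters table limits the second lavage in the same way: "Only applicable to participants who undergo neoadjuvant therapy".
- Section 5b: "For patients who have undergone neoadjuvant therapy, a further peritoneal lavage will be performed at surgical resection".
- Scale of the genomic results, section 5a: "resulting in a binary output of positive or negative for the presence of ptDNA and ctDNA, respectively".

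The methylomic ptDNA result is also reported as positive or negative.

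**The concern.** Every lavage at resection comes from a patient who also has a planned lavage at staging, so the before/after comparison is a paired comparison of two binary results. Plasma and lavage fluid are likewise taken from the same patients at staging.

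The named methods have two ordinary readings, and neither answers the before/after question.

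1. A chi-square test comparing the two rates treats them as independent samples and uses the wrong standard error for their difference.
2. A chi-square test, or a Pearson correlation (which is phi for two binary variables), on the paired 2x2 table asks whether the two results are associated. It does not ask whether the rate changed.

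At stake is the answer to two listed exploratory objectives (2 and 4), which rest on research blood and lavage taken in addition to standard care. A real change in detection could be missed under the first reading. Under the second, association could be reported as if it were change.

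A lesser issue concerns denominators. A staging sample is planned for everyone, but a resection sample exists only for neoadjuvant patients who reach surgery. Section 8b does not say that the before rate is restricted to patients with both.

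**Working it through.** **Plan's own figures.** The protocol gives no sample size, rate or power for the exploratory analyses. Its only design figure, 175 + 25 = 200, belongs to the primary comparison (70% versus 40% DFS). It is reproduced by a two-sided Fisher test (exact power 80.9%) and has no bearing here.

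**Inputs.** Detection before therapy is set at 36%, from the pilot result of 4 in 11 (section 3c). The following are not in the protocol and are assumed: 24% after therapy; 100, 150 or 200 complete pairs; within-patient correlation phi from 0 to 0.7.

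**Reading 1: chi-square on the two rates.** The variance of the difference in paired proportions is

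[p1(1−p1) + p2(1−p2) − 2·phi·√(p1(1−p1)p2(1−p2))]/n.

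The unpaired test drops the phi term. With equal rates, the true standard error is √(1−phi) times the one the test uses. The real type I error of a nominal 5% test is therefore P(|Z| > 1.96/√(1−phi)):

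- phi 0.3: 1.96/0.837 = 2.34, giving 1.9%
- phi 0.5: 1.96/0.707 = 2.77, giving 0.6%
- phi 0.7: 1.96/0.548 = 3.58, giving 0.04%

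Simulation (40,000 runs per row, asymptotic McNemar test) agrees and adds power:

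| Pairs | phi | Unpaired type I error (36% both times) | Unpaired power (36% vs 24%) | McNemar power |
|---|---|---|---|---|
| 100 | 0 | 4.9% | 46% | 45% |
| 100 | 0.3 | 2.0% | 45% | 60% |
| 100 | 0.5 | 0.6% | 44% | 76% |
| 100 | 0.7 | 0.04% | 42% | 95% |
| 150 | 0 | 5.0% | 62% | 62% |
| 150 | 0.5 | 0.6% | 67% | 90% |
| 200 | 0 | 5.1% | 75% | 75% |
| 200 | 0.5 | 0.6% | 83% | 96% |

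McNemar's type I error stayed between 4.7% and 5.4% throughout.

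**The same point on one table.** Take 100 pairs, 36 positive before and 24 after. The unpaired statistic does not depend on the overlap: 0.12²/(2 × 0.30 × 0.70/100) = 3.43, p = 0.064. McNemar's statistic is (36−24)²/(60 − 2a), where a is the number positive both times.

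| a | McNemar statistic | p | Exact p |
|---|---|---|---|
| 9 | 144/42 = 3.43 | 0.064 | 0.088 |
| 16 | 144/28 = 5.14 | 0.023 | 0.036 |
| 20 | 144/20 = 7.20 | 0.0073 | 0.012 |
| 24 | 144/12 = 12.0 | 0.0005 | 0.0005 |

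At lower assumed rates the pattern is the same. With 20 positive before and 11 after (10 cleared, 1 converted), unpaired p = 0.079 and exact McNemar p = 0.012.

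**Reading 2: association on the paired table.** Take 100 pairs, 20 positive before, 20 after, 14 both times, so no change at all. Then phi = (14 × 74 − 6 × 6)/(20 × 80) = 0.625, chi-square = 100 × 0.625² = 39.1 and p = 4 × 10⁻¹⁰. Exact McNemar p = 1.0. In simulation with no change (36% both times, phi 0.5, n = 100), the association test was significant in 99.9% of runs. With a real fall from 36% to 24% but phi 0, it was significant in only 5.0%.

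**Denominators.** Section 5a plans a staging lavage for all patients and a resection lavage for the neoadjuvant subset. Section 8a allows for 30% attrition without saying when or why it occurs. An unpaired comparison can be run on two different sets; a test on complete pairs cannot.

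**The case against.** The strongest reply is that one loose sentence covers four unlike analyses, assigns no test to any of them and ends with an open category. McNemar's statistic is itself referred to a chi-square distribution, and the exact form of an exploratory test is often left to the analysis plan. Part of this stands: a paired test is not strictly excluded. But chi-square tests listed beside Pearson correlations do not tell an analyst to use one, and the open category is called qualitative. The protocol has named methods, and in their ordinary form they do not fit its own data.

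Several stronger readings are tempting and are not supported.

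- A reader might infer that the protocol will compare all patients before with a subset after. It does not say so, and its reference to neoadjuvant therapy points to the patients who received it. Different denominators are permitted, not planned.
- A reader might infer that the rate comparison would produce false positives. With positive correlation it does the opposite.
- A reader might infer that the whole ptDNA-versus-ctDNA analysis is invalid. Testing each marker separately against recurrence site by chi-square is sound. Pairing matters only where the two markers are contrasted directly.
- A reader might infer that Pearson correlation is meant for agreement between binary calls. Section 4c also lists mutant allelic frequency measures for both markers, so that use is not shown.
- Genomic versus methylomic assay performance is a secondary objective with its own metrics. Only the cost-effectiveness side of that comparison falls under the quoted sentence.

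**Conclusion.** The point holds in a limited form. Section 8b names methods that, used in the ordinary way, do not test a within-patient change in detection rate or a within-patient difference between two markers. Read as a comparison of rates, the chi-square test costs power: nothing at phi 0, but at 100 pairs 44% instead of 76% at phi 0.5 and 42% instead of 95% at phi 0.7. Read as a test on the paired table, it answers a different question.

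These sizes are illustrations. They assume the number of pairs, the rate after therapy and a positive within-patient correlation, none of which the protocol gives. The power figures are for the asymptotic McNemar test; the worked table shows that the exact version gives somewhat larger p-values in most cases. Severity is minor: the analyses are exploratory, the paired data will exist whatever test is named, and the primary endpoint and the 200-patient target are unaffected.

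**What to change.** Amend section 8b as follows.

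- Make the before/after comparison in neoadjuvant patients with both samples, by McNemar's exact test, with the paired difference in detection rate and its confidence interval.
- Report how many neoadjuvant patients have no second sample and their baseline ptDNA rate, so that selection of those who reach surgery can be seen.
- Where ptDNA and ctDNA are formally contrasted as predictors of recurrence, use a paired comparison: McNemar's test for sensitivity and specificity, or a paired difference in AUC.

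The cost is a few lines of text. No further patients, samples or data are needed.
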